## Methods

### Study Design

This is a phase III, single-center, pragmatic randomized controlled trial (RCT) to evaluate if a patient-centric self-monitoring and collaborative decision support platform will lead to sustainable improvement in overall QOL for IBD patients. It is intended that 300 patients with IBD will be recruited into the study (allocation ratio 1:1; Figure 4). After meeting all the inclusion criteria with no exclusions, patient is asked to complete a tablet-based screening questionnaire at the end of which patient is randomized at the point of care to intervention or control arm. Patients in the control arm will receive an IBD education app PIN whereas the intervention arm will receive HealthPROMISE app PIN (Figure 3). Intervention patients enter their data once every 2 weeks and this data is then made visible to providers using a Web-based dashboard integrated with the EHR (Figures 4 and 5). Intervention and control apps will be provided free of charge to patients, and patients will be given $25 after completing initial and end of study questionnaires.

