#### Sample Size Justification

Study endpoints will be primarily assessed using intention-to-treat (ITT) analysis; however, per-protocol analysis will also be performed. The study is to be powered such that there is a>80% probability of demonstrating a difference with a *P* value *(P* = .05) using a two-tailed *t* test.

We assume that 128 out of 150 subjects (85%) in the intervention arm will meet all quality indicators (primary outcome) and expect that this percentage will be at least 15% lower in the control arm. A sample size of 95 patients will be needed in each arm to achieve at least 80% power to detect the difference with a 5% one-sided significance level.

Accounting for an estimated 30% attrition rate, we will require a total of 250 IBD patients to be enrolled in the study. Since some patients may agree to enroll but not download the app or use the PIN, we will recruit a total of 300 patients in the study.

For secondary outcomes related to QOL, the control arm is not a placebo arm and physicians are free to initiate any therapy based on patients' symptoms. Hence, we will assess the difference in proportion of patients achieving MCID in the HealthPROMISE arm versus control arm in the study. Using the distribution-based approach, an effect size of 0.5 SD is the closest estimate for determining MCID for SIBDQ and EQ-5D. Assuming that 20% more patients in HealthPROMISE arm will achieve MCID than in the control arm, the sample size of 250 patients will have 88% power to detect the difference with a 5% one-sided significance level and an estimated 30% attrition rate.

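### The 250 patients said to allow for 30% attrition should be 272, and whether the 300 recruited secure 80% power depends on how app non-users are counted, which the plan leaves open

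*Protocol article*

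**What the plan says.** All the sizing figures are in the protocol article, Sample Size Justification.

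- **Rates.** "We assume that 128 out of 150 subjects (85%) in the intervention arm will meet all quality indicators", and the authors "expect that this percentage will be at least 15% lower in the control arm".
- **Evaluable number.** "A sample size of 95 patients will be needed in each arm to achieve at least 80% power". The level for this calculation is one-sided 5%.
- **Attrition step.** "Accounting for an estimated 30% attrition rate, we will require a total of 250 IBD patients to be enrolled in the study".
- **Step to 300.** "Since some patients may agree to enroll but not download the app or use the PIN, we will recruit a total of 300".
- **Analysis population.** "Study endpoints will be primarily assessed using intention-to-treat (ITT) analysis", with a per-protocol analysis in addition.

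Under Study Design, allocation is 1:1 and the "patient is randomized at the point of care to intervention or control arm"; the PIN handed out is the one for the assigned arm's app. A patient who never uses the PIN has therefore already been randomized.

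The last paragraph of Sample Size Justification uses 250 again. It claims 88% power for a 20-point difference in the proportion reaching the minimal clinically important difference in quality of life (QOL), one-sided 5%, after 30% attrition.

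**The concern.** The attrition step should return a number which, after 30% are lost, still leaves 95 per arm. It does not, so a required sample size printed in the primary power justification is wrong on the plan's own inputs.

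The target of 300 is larger than the correct number, but the plan gives a different reason for the added 50. It treats app non-use as something to cover with more patients. Under a primary intention-to-treat analysis, non-use among randomized patients is a question about effect size rather than headcount, and the article does not say whether its 85% already reflects it. A reader cannot tell whether the 300 secure the intended 80%.

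**Working it through.** **Inputs** (Sample Size Justification): intervention 85%; control 70%, reading the 15% as percentage points; one-sided 5%; 80% power; attrition 30%; enrollment 250, then 300. Allocation 1:1 (Study Design).

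**1. Reproduce the 95 per arm.** Normal approximation with pooled variance under the null, no continuity correction:

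n = [1.645 × √(2 × 0.775 × 0.225) + 0.842 × √(0.85 × 0.15 + 0.70 × 0.30)]² / 0.15²

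= (0.971 + 0.489)² / 0.0225 = 94.8, so 95. The plan's figure reproduces exactly, which also confirms the percentage-point reading: a relative 15% (control 72.25%) would need 127 per arm.

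**2. Attrition step.** Required total = 2 × 95 / (1 − 0.30) = 190 / 0.70 = 271.4, so 272 (136 per arm). Multiplying instead, 190 × 1.30 = 247, which rounds up to 250. The stated 250 would be right for 1 − 190/250 = 24% attrition, not 30%.

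**3. Power at each enrollment figure**, 85% v 70%, one-sided 5%:

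Power = Φ{[0.15√n − 1.645 × √(2 × 0.775 × 0.225)] / √(0.85 × 0.15 + 0.70 × 0.30)}

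| Enrolled | Left after 30% loss | Per arm | Power |
|---|---|---|---|
| 250 | 175 | 87.5 | 77.1% |
| 272 | 190.4 | 95.2 | 80.2% |
| 300 | 210 | 105 | 83.5% |

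**4. What the extra 50 do.** There are two ways to treat patients who never take up the app.

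- *Set aside.* If all 50 go, 250 remain; 30% attrition leaves 87.5 per arm and power is 77.1%.
- *Kept under intention-to-treat.* They count toward the sample, so 300 gives 105 per arm. Assume a share f of the retained intervention patients are non-users who respond like controls, and that the 85% describes users only. The intervention rate is then 0.85 − 0.15f:

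| Non-users f (assumed) | Intervention rate | Power at 105 per arm |
|---|---|---|
| 0 | 85.0% | 83.5% |
| 5% | 84.25% | 79.5% |
| 10% | 83.5% | 75.2% |
| 1 in 6 (50/300) | 82.5% | 68.7% |

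Power is exactly 80% at f of about 4.4%, roughly 7 of 150 intervention patients if users and non-users are lost equally.

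**5. The QOL statement.** 250 × 0.70 = 175, or 87.5 per arm. The control proportion is not given, so it has to be assumed. For a 20-point difference, one-sided 5%, power is 89.8%, 87.6%, 86.0% and 84.6% at control proportions of 20%, 25%, 30% and 40%. The stated 88% is attainable near a 25% control proportion. At 95 per arm, a control proportion of 30% or 50% would give 88.4%. The text does not say which route was taken.

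**The case against.** The strongest reply is that 250 is only an intermediate figure. The article sets recruitment at 300 in the Abstract, Study Design, Table 1 and Sample Size Justification, and 300 with 30% attrition leaves 105 per arm, above the 95 required. This stands: the adopted target is not too small for attrition alone, and only the intermediate figure is wrong.

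A reader might go further and infer that the extra 50 cannot restore power because intention-to-treat keeps them in the analysis. That does not follow. Patients who are kept add to the analysed number; only dilution of the effect could lower power. Dilution is not established either. The 85% is written as 128 of 150, and 150 is the whole intervention arm of a 300-patient trial, so it can be read as a rate over everyone randomized. Lowering it further would then count non-use twice. The article also gives no expected non-user share and no overlap with the 30% attrition, and non-users may well be among those lost. The 1-in-6 row is therefore an assumption, not the plan's forecast.

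A reader might also infer that the plan invites exclusion of non-downloaders after randomization. The documents do not support this: intention-to-treat is named as primary, per-protocol is separate, and nowhere are non-downloaders said to be excluded or replaced. Nor is the 88% QOL power shown to be wrong. The article's mention of a two-tailed test beside a one-sided level is a separate conflict and is not used here.

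None of this rescues 250 as the number needed for 95 per arm at 30% attrition.

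**Conclusion.** The arithmetic error is certain and rests only on the plan's own figures: 272, not 250, a shortfall of 22 patients. Power at 250 is 77.1% against the stated 80%.

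For the trial as recruited, the consequence is conditional. At 300, one-sided power is 83.5% if the 15-point difference holds across all randomized patients. It falls below 80% only if more than about 4.4% of retained intervention patients are non-users, those patients respond like controls, and the 85% does not already include them. The article settles none of these points, so a flat statement that 80% is missed would claim too much. So would a statement that the 300 settle the matter, because the text commits the added 50 to non-use and not to the attrition shortfall.

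**What to change.** In Sample Size Justification:

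1. Replace 250 by 272, showing 190/0.70.
2. Keep recruitment at 300, and state that all randomized patients belong to the intention-to-treat comparison whether or not they take up the app.
3. State whether the 85% is a rate over all patients randomized to the intervention or over users only.
4. Give power at 300 as a range with its assumption shown. If non-users respond like controls: 83.5% with none, 79.5% with 5%, 75.2% with 10%, 68.7% with 1 in 6, and 80% at about 4.4%. If the 85% already includes non-users, say so and quote 83.5%.
5. Check the 88% QOL power against 175 evaluable patients and state the assumed control proportion.

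The cost is one corrected figure and a few sentences. Recruitment does not change. The downside is that the stated power becomes slightly less favourable wherever dilution is allowed for.

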### Statistical Analysis Plan

#### Overview

We will use SAS 9.2 (SAS Institute, Inc) to calculate frequencies and percentages for categorical factors and means with standard deviations and/or percentiles for continuous factors. Pearson’s chi-square tests will be used for primary outcome (number of quality indicators met in HealthPROMISE vs control arm) and secondary outcomes. We will calculate percentage score for each patient at baseline and at week 104 ([number of quality metrics met/quality metrics eligible]*100). Change in the percentage score from baseline to week 104 will be aggregated for each arm to calculate percentage-point improvement in quality metric, similar to the strategy by Cebul et al [26].

Analysis of covariance (ANCOVA) will be performed to assess differences in the area under the curve of QOL scores while adjusting for baseline QOL score. To assess the association between patient and practice characteristics and achievement of eligible quality metrics, we will use multivariable analyses. Since the data will be hierarchically structured, with patients clustered within physicians and metrics clustered within patients, we will construct multilevel, generalized, linear mixed models with random effects to determine predictors of quality care, similar to the strategy used by Kanwal et al [27]. Independent variables will include demographic characteristics (age, gender), education and income level, race and ethnicity, computer usage, eHealth literacy scores, clinical characteristics (comorbidities, phenotype, disease severity), and provider characteristics (gender, age, site of practice, years of practice, presence of nurse practitioner).

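### The powered quality-of-life comparison is a split at the MCID, justified by a reason that does not support splitting; a like-for-like ANCOVA of exit score on baseline should be named as the main analysis

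*Protocol article*

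**What the plan says.** Three parts of the protocol article deal with the between-arm QOL analysis.

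- **Sample Size Justification.** The premise is that "the control arm is not a placebo arm and physicians are free to initiate any therapy based on patients' symptoms", and from it follows "Hence, we will assess the difference in proportion of patients achieving MCID in the HealthPROMISE arm versus control arm in the study". The threshold is distribution-based: "an effect size of 0.5 SD is the closest estimate for determining MCID for SIBDQ and EQ-5D". Power is then given, for a responder proportion 20 points higher with HealthPROMISE: "the sample size of 250 patients will have 88% power to detect the difference with a 5% one-sided significance level and an estimated 30% attrition". No control-arm responder rate is stated. The same section opens by powering the study on a test described as "using a two-tailed *t* test".
- **Statistical Analysis Plan, Overview.** Pearson's chi-square is named for the secondary outcomes. Separately, ANCOVA is to "assess differences in the area under the curve of QOL scores while adjusting for baseline QOL score".
- **Outcome Measures.** The listed QOL endpoints are change from baseline in EQ-5D and general QOL scores by group. No MCID-responder endpoint is listed.

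Under Disease Specific Quality of Life Questionnaire, both arms complete SIBDQ at baseline and exit, and only the intervention arm is also asked for it every 2 weeks. Under General Quality of Life Questionnaire, EQ-5D is requested every 2 weeks in the intervention arm, with no schedule given there for controls.

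**The concern.** The inference from a non-placebo control to a responder analysis does not follow. Free treatment in the control arm may shrink the difference between arms, but it shrinks a difference in means and a difference in responder proportions alike. The article gives no other reason for the split.

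Dichotomising a score discards information, so the test that carries the QOL power statement is less efficient than the collected data allow. The planned ANCOVA would repair this, but its outcome is an area under the curve. As scheduled, that area would be built from many scores in one arm and two in the other, so it would not measure the same thing in both arms. QOL is formally secondary, yet the Objective and Study Design sections word the trial's hypothesis as sustained improvement in overall QOL. It therefore matters which analysis answers that question and how well.

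**Working it through.** **Inputs from the protocol article.** 250 enrolled, 30% attrition, 1:1 allocation, 20-point responder difference, 5% one-sided. Evaluable: 250 × 0.70 = 175, or 87.5 per arm.

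**Assumptions (not in the article).** Control responder rate c, ranged over 20-60%. Change scores normal with equal SD, and the effect a uniform shift. Baseline-exit correlation r, ranged over 0.3-0.7.

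**Step 1: reproduce the stated 88%.** With p₁ = c + 0.20, p̄ the mean of the two rates and n = 87.5:

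power = Φ{ [0.20 − z·√(2p̄(1−p̄)/n)] / √[(p₁(1−p₁) + c(1−c))/n] }

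At c = 25% and z = 1.645: [0.20 − 1.645 × 0.0721] / 0.0705 = 1.154, so power is 87.6%. The stated figure reproduces within 2 points for control rates of about 20-30% or 50-60%. Near 40% it falls to 84.6%.

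**Step 2: put the same effect on the score scale.** The shift in SDs of change is d = Φ⁻¹(c + 0.20) − Φ⁻¹(c). Mean-change power is Φ(d·√(n/2) − z). At c = 25%, d = 0.549 and √(87.5/2) = 6.614, so 0.549 × 6.614 − 1.645 = 1.986 and power is 97.6%.

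**Step 3: ANCOVA of exit on baseline.** The SD of change is σ√(2(1−r)) and the ANCOVA residual SD is σ√(1−r²). Their ratio is √((1+r)/2), so d is divided by that factor. At c = 25% and r = 0.5: 0.549/0.866 × 6.614 − 1.645 = 2.55, and power is 99.5%.

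Results at 87.5 per arm (ANCOVA columns run from r = 0.7 to r = 0.3):

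| c | d | Responder, 1-sided | Mean change, 1-sided | ANCOVA, 1-sided | Responder, 2-sided | Mean change, 2-sided | ANCOVA, 2-sided |
|---|---|---|---|---|---|---|---|
| 20% or 60% | 0.588 | 89.8% | 98.8% | 99.5-99.9% | 82.9% | 97.3% | 98.8-99.8% |
| 25% | 0.549 | 87.6% | 97.6% | 98.9-99.8% | 79.7% | 95.3% | 97.6-99.4% |
| 30% or 50% | 0.524 | 86.0% | 96.6% | 98.3-99.6% | 77.5% | 93.4% | 96.4-99.0% |
| 40% | 0.507 | 84.6% | 95.6% | 97.7-99.4% | 75.8% | 91.8% | 95.3-98.6% |

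At c = 25%, 88% one-sided power needs 89 per arm for the responder test, 53 for mean change and 35-45 for ANCOVA. The ratios are 89/53 = 1.7, and 89/45 = 2.0 to 89/35 = 2.5.

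**Step 4: what the area under the curve becomes on shared time points.** With scores only at baseline B and exit E over time T, the trapezoid area is T(B + E)/2. Adjusted for B, the arm effect is T/2 times that from ANCOVA of E on arm and B, with the same test statistic and P value. Restricting the planned analysis to shared SIBDQ time points therefore turns it into the analysis recommended here.

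**The case against.** A reader might infer that the trial analyses QOL only by dichotomising, that baseline is ignored, or that the responder test is the only workable comparison. The article does not support any of these. It plans a baseline-adjusted ANCOVA of QOL scores and lists change in EQ-5D as an endpoint. General Quality of Life Questionnaire describes the MCID as a change, so reaching it is itself measured from baseline; what the responder test lacks is covariate adjustment. Step 4 also shows that the planned ANCOVA can be rescued simply by limiting it to shared time points.

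Nor does the article support calling the responder test underpowered. At its stated one-sided level, power is 85-90%, above the 80% target. If all 300 planned recruits are counted and 30% are lost (105 per arm), it is 90-94% one-sided and 83-89% two-sided. The shortfall below 80% at 87.5 per arm appears only with a two-sided test, and the conflict over sidedness is a separate matter.

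The gain also depends on the normal-shift model. It shrinks if scores are skewed or near a ceiling, or if only a subset of patients benefits. A proportion reaching MCID is easy to interpret and worth reporting.

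All of this stands and limits the point. It does not supply a reason for the split, make the two arms' areas comparable as scheduled, or say which analysis decides. The Abstract has controls entering data at office visits as well, but does not say that this includes SIBDQ, and visit timing need not match a fortnightly schedule.

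**Conclusion.** The point holds in a limited form. The reason given for a responder analysis does not support it, the planned ANCOVA is not like for like under the stated SIBDQ schedule, and the article does not rank its QOL analyses or list the one it powers.

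At the same control rate, the responder test gives up about 9-11 points of power to mean change one-sided and 14-16 points two-sided; against ANCOVA the loss is larger. These sizes rest on a normal shift, 87.5 evaluable per arm, an assumed control rate of 20-60% and, for ANCOVA, an assumed correlation of 0.3-0.7. This is an inexpensive improvement to a secondary analysis. It does not show that the trial is too small.

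**What to change.** - Name ANCOVA of the exit SIBDQ score on arm and baseline SIBDQ as the main between-arm QOL analysis, and state the exit week, since the article gives 52 or 104. Do the same for EQ-5D where both arms supply it.
- Restrict any area-under-the-curve analysis to time points scheduled in both arms. Fortnightly intervention-arm scores can be described within that arm.
- Keep the proportion reaching MCID as a supportive summary, add it to the endpoint list in that role, and drop the argument from the non-placebo control.
- Rewrite the QOL power statement for the ANCOVA, stating the assumed difference, SD, correlation and sidedness.

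For SIBDQ this needs no new data and no more patients. The cost is that the responder proportion is no longer the main QOL test and the stated 88% has to be replaced.

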## Discussion

### Principal Findings

This pragmatic trial will help us study if a patient-centric self-monitoring and collaborative disease management app and dashboard can lead to improvement in care provided to IBD patients. Our hypothesis is that IBD patients using the HealthPROMISE platform will have significant improvement in QOC metrics, QOL, and resource utilization by the end of the 2-year study period when compared to IBD patients in the control arm (using a health education app alone).

### Future Direction and Sustainability

HealthPROMISE can be a sustainable platform in the long run because it is patient-centric, device and disease agnostic, and not dependent on proprietary EHRs. As most of the data is entered by patients, the cost of running, supporting, and sustaining HealthPROMISE is very low compared to traditional disease registries. HealthPROMISE has a rapid form generator capability to allow it to be customized for other chronic diseases. Additionally, the decision support that generates alerts and dashboard reports is within the stand-alone HealthPROMISE app and not dependent on proprietary EHRs. We aim to integrate HealthPROMISE with personal health records, partner with national societies, and support through consortia so it can become a new standard of quality care for IBD and other chronic diseases.

### Conclusion

HealthPROMISE is a unique cloud-based PRO and decision support tool that empowers both patients and providers. Patients track their QOL and symptoms, and providers can use the visual data in real time (integrated with EHRs) to provide better care to their entire patient population. Using pragmatic trial design, we hope to show that IBD patients who participate in their own care and share in decision making have appreciably improved outcomes when compared to patients who do not [28,29].

## Abbreviations

IBD: inflammatory bowel disease
QOL: quality of life
QOC: quality of care
PRO: patient-reported outcome
EHR: electronic health records
NIH: National Institutes of Health
RCT: randomized controlled trial
SIBDQ: Short Inflammatory Bowel Disease Questionnaire
MCID: minimal clinically important difference
PAM: patient activation measure
